#### Experimental endpoints

The following experimental pain measures will be employed prior to intervention as well as 24–48 h and 3 months after intervention to characterize changes in pain processing induced by the assigned procedures:
Muscle pressure stimulation (pancreatic viscerotome [T10 ventral and dorsal] and control areas [C5, L1 and L4])Bone pressure stimulation (tibia bone)Temporal summation to repetitive pinprick stimulations of the pancreatic area (T10) and control area [dominant forearm])Conditioned pain modulation (CPM)

### Sample size determination

The study is powered to detect a minimal difference between groups of 30% in the average clinical pain score 3 months after intervention [34]. On the basis of an assumed SD of 45%, we determine that a study with 48 patients per group is needed to provide power of 90% (to allow secondary endpoints) with the use of a two-sided significance level of 0.05 [35]. To allow a 10% dropout rate, the sample size is set at 106 patients.

### Randomization, blinding, and treatment allocation

Randomization is performed using an automatic assignment system that conceals allocation. Block randomization is employed with randomization of six patients per block to equal proportions for sham procedures or combined ESWL and endotherapy. No stratification of randomization based on demographic or clinical variables will be applied. The allocation sequence will be generated by a biostatistician who will not be involved in the administration of treatment or recording of data. Randomization of patients into the two groups will be done by a physician who will not have access to the clinical data of the patients.

The patients will be blinded to the treatment received. The patients in the sham procedure will be provided a superficial needle prick with a sterile needle to mimic epidural anesthesia. Then the ESWL instrument will be started so that the patients get an auditory perception that the treatment is being provided. The patient’s eyes will be covered, and if the patient wishes, he or she will be given light sedation. The operator cannot be blinded, owing to the nature of the study. However, the principal investigator and the statistician will be blinded to the treatment arms.

In case of an emergency that necessitates knowledge of the procedure allocation, the individual procedure assignment for each patient will be available. The codes will be available at the study center in sealed envelopes that are stored in a locked and secured area accessible only to those individuals authorized by the investigator. This procedure allows unblinding of individual subjects, without revealing codes of the entire study. The investigator will be able to determine which procedure a patient was given by opening the sealed envelope with the corresponding randomization number. The investigator must state the reason why the code was broken on the envelope and must date and sign it. At the end of the study, all sealed and unsealed envelopes must be accounted for.

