### Study design and setting

We are conducting a randomized, single-blind, single-center, parallel-group, sham-controlled, prospective trial designed to evaluate the effect of combined ESWL and endoscopic treatment for pain in adult patients with CP. The study will be conducted at the tertiary care academic Asian Institute of Gastroenterology in Gachibowli, Hyderabad, India.

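### A fixed, published block size of six at a single centre with unblinded operators would let anyone who tracks past allocations deduce about a quarter of assignments

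*Protocol article*

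**What the plan says.** The section Randomization, blinding, and treatment allocation gives one block size and an equal split: "Block randomization is employed with randomization of six patients per block to equal proportions". It adds that "No stratification of randomization based on demographic or clinical variables will be applied". The section Study design and setting describes a "randomized, single-blind, single-center, parallel-group, sham-controlled, prospective trial". Together these define one allocation sequence at one site, in constant blocks of three active and three sham.

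On knowledge of treatment, the same section says "The operator cannot be blinded, owing to the nature of the study".

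It also names four safeguards:
- "Randomization is performed using an automatic assignment system that conceals allocation";
- "The allocation sequence will be generated by a biostatistician who will not be involved in the administration of treatment or recording of data";
- the physician who randomizes has no access to patients' clinical data;
- the principal investigator and the statistician are blinded to arm.

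The article does not say that block sizes vary or that the size is withheld from site staff. It was published on 16 April 2020. Under Trial status, the first patient was randomized by 4 January 2020 and recruitment was expected to finish on 1 July 2021.

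**The concern.** With a known, constant block size, the end of each block can be worked out from its beginning. Once three patients in a block have gone to one arm, the rest must go to the other. A concealed list does not prevent this, because the deduction uses only allocations already made. With one centre and no strata there is one sequence to follow, and the operators see the arm of each patient they treat. The block size was published with more than 14 months of planned recruitment left.

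What is at stake is selection at entry. Two exclusion criteria rest on the investigator's judgement: laboratory abnormalities, and other disease of importance for the study. The active procedures are in daily clinical use (Monitoring and safety) and invasive treatment is recommended in guidelines (Discussion), so staff may have a view on who should not receive sham. If someone who could foresee the next arm also influenced whether or when a patient entered, the arms could differ at baseline. Adjustment would deal only with the measured part of such a difference. The primary outcome is self-reported pain, and the trial presents itself as the first sham-controlled evidence on this question, so credible concealment matters here.

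**Working it through.** **Inputs.** Block size 6, split 3:3, no strata (Randomization, blinding, and treatment allocation); one centre (Study design and setting); 106 patients (Sample size determination). The article gives no predictability figure to reproduce. Its total does reproduce: 48 per group gives 96, and 96 × 1.10 = 105.6, rounded up to 106.

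**Assumed observer.** Someone who knows the block size, where each block starts, and every earlier allocation in the block.

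**Certain allocations per block.** A 3:3 block has 6!/(3!·3!) = 20 equally likely orders. An allocation is certain when one arm's three places are already used. The best guess is the arm with more places left.

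| Position in block | Probability that it is certain | Probability that the best guess is right |
|---|---|---|
| 1 | 0 | 0.50 |
| 2 | 0 | 0.60 |
| 3 | 0 | 0.60 |
| 4 | 2/20 = 0.10 | 0.70 |
| 5 | 8/20 = 0.40 | 0.70 |
| 6 | 1.00 | 1.00 |
| Sum | 1.5 of 6 (25.0%) | 4.1 of 6 (68.3%) |

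Two checks on the 1.5:
- The closed form 2m/(m+1) with m = 3 gives 6/4 = 1.5.
- Of the 20 orders, 12 leave one certain allocation, 6 leave two and 2 leave three: (12×1 + 6×2 + 2×3)/20 = 30/20 = 1.5.

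**Over the trial.** 106 = 17 × 6 + 4.
- Certain: 17 × 1.5 + 0.10 = 25.6, and 25.6/106 = 24.2%. (Taking 106/6 blocks times 1.5 gives 26.5, which wrongly credits the last, four-patient block with a full share.)
- Best guess right: 17 × 4.1 + (0.50 + 0.60 + 0.60 + 0.70) = 72.1, and 72.1/106 = 68.0%.

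**Effect of varying the block size.** This was simulated over 1,500 trials of 106 patients, with each block's size drawn with equal probability from a set. The observer knows the set and all past allocations, and updates by Bayes' rule. The sets are assumptions, since the article names none.

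| Block sizes | Certain | Best guess right |
|---|---|---|
| 6 only | 24.2% | 68% |
| 4, 6 | 5.5% | 69% |
| 4, 6, 8 | 2.2% | 68% |
| 6, 8, 10 | 1.6% | 66% |

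Varying the size removes most of the certainty and hardly any of the guessing advantage.

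**Balance.** Wherever recruitment stops, the largest difference between arms is half the largest block: 3 with blocks of 6, and 4 when blocks of 8 are included. If recruitment stops at exactly 106 under fixed sixes, the difference is at most 2, because the last four patients can split no worse than 3:1.

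**The case against.** A reader might infer that one in four allocations is certain in advance, that operators know the whole sequence so far, and that concealment has failed. The document does not support this. The quarter is certain only to the observer assumed above. The article says that the operator cannot be blinded. It does not say how many operators there are, whether ESWL and ERCP share one, or whether anyone follows the running sequence. If several share the cases, none automatically sees a whole block.

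Harm also needs foresight and control of entry to meet, in one person or through communication. The discretionary criteria belong to the investigator, whereas the unblinded person is the operator, and the principal investigator is blinded. No passage says that operators screen, judge eligibility or enrol. A journal article commonly leaves such roles to the full protocol, so silence cannot be read as overlap. The randomizing physician, lacking clinical data, cannot match a foreseen arm to a patient's profile. Several entry criteria are concrete (age, pain score and frequency, duct obstruction on imaging, no previous pancreatic surgery, ESWL or ERCP), which leaves less room to steer.

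All of this stands, and it limits the point to a conditional one. It does not dispose of it: none of the four safeguards blocks inference from past allocations, and the constant block size is a stated design choice, not a missing detail.

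**Conclusion.** The point holds as an avoidable weakness in the allocation scheme. It is not evidence that selection bias occurred. For a person who knows the block boundaries and all earlier allocations, about 24% of assignments (25.6 of 106) are deducible, and 68% can be guessed against 50% by chance. These figures are exact under that assumption and 3:3 blocks throughout. Whether such a person also influences entry cannot be settled from the article, so no size can be put on any bias in the pain outcome, and none is claimed. The case for acting is that the exposure can be greatly reduced at almost no cost, and that recruitment was still under way when the block size was published.

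**What to change.** 1. Have the independent biostatistician regenerate the unused part of the sequence with block sizes varying at random, for example 4, 6 and 8, starting once the block in use is complete. Keep the sizes and their set from site staff and operators, and out of print, until recruitment ends. The fall to about 2% certain allocations applies only to patients randomized under the new sequence.
2. Because this leaves the best-guess rate near 68%, add one sentence to the protocol: those who screen, judge eligibility or schedule entry have no access to past allocations. If operators now do any of these tasks, separate the roles.

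The cost is a short task for the biostatistician, a documented change, and a possible final imbalance of at most 4 patients instead of 3. Sample size, endpoints and patient procedures are unaffected. Separating roles may take some organization at a single site, depending on who now does what.

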#### Combined ESWL and endoscopic treatment

Patients enrolled in the active treatment group will be subjected to ESWL followed by ERCP. In India, patients with CP typically present with large pancreatic stones that tend to be dense and spiculated. In order to ensure complete stone clearance, ESWL and ERCP are therefore performed together and in agreement with clinical practice in most centers [10, 31].

ESWL will be conducted with the patient under epidural anesthesia. For epidural anesthesia, bupivacaine will be used to block the T6–T12 thoracic spinal segments. The patient’s eyes will be lightly covered during the procedure. Once epidural anesthesia is achieved, the patient will be given a light sedation, and ESWL will be performed using a third-generation Dornier dual focus lithotripsy system (Dornier Delta 3; Dornier MedTech GmbH, Weßling, Germany), providing a maximum of 5000 shocks at the rate of 90 shocks per minute. If complete stone clearance is not achieved during the first ESWL session, a second session will be scheduled the following day.

After lithotripsy, stone fragments will be removed during an ERCP procedure. An endoscopic pancreatic sphincterotomy will be performed, and complete stone removal will be attempted with registration of pancreatic duct clearance. If cannulation fails after a maximum of five attempts, the patient will be subjected to precut sphincterotomy. In case a pancreatic duct stricture is identified during the ERCP procedure that was not detected by MRCP prior to enrollment, the stricture is dilated and followed by pancreatic stent insertion. A pancreatic duct stent will also be inserted in case of incomplete stone removal during the ERCP procedure.

Patients undergoing pancreatic duct stenting will be referred for a new ERCP procedure after 6 months for stent exchange or removal (after completion of all study assessments). When complete runoff of contrast material is observed after removal of the stent and an extraction balloon can be passed through the pancreatic duct, endoscopic treatment is considered completed, and further stenting will be stopped. Persistent strictures will be treated by repeated endoscopic dilations and sequential insertion of new stents in agreement with the European Society of Gastrointestinal Endoscopy guidelines [32].

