#### Sham treatment

In the sham/control group, patients will be given a transient superficial pinprick sensation to give the feeling of epidural anesthesia prior to sham ESWL. Subsequently, the lithotripsy machine will be switched on, without establishing any form of contact with the patient’s body. The patient’s eyes will be lightly covered during the entire procedure. Following sham ESWL, patients will be subjected to sham ERCP with duodenal intubation of the endoscope and examination of the papillary area, but no pancreatic ductal intervention will be performed.

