#### Primary clinical endpoint

The primary clinical endpoint is pain relief. Average and maximal daily clinical pain intensity scores will be recorded in a patient pain diary based on a 0–10 VAS, with registration of the baseline pain intensity scores done in the week prior to intervention and weekly recordings continued for a 3-month period after intervention. Mean values of pain scores will be calculated over 1 week to adjust for day-to-day variability in pain intensity. The difference in pain scores between patients receiving active treatment (ESWL and ERCP) and sham treatment are compared, with the primary comparison of average pain scores 3 months after intervention. Weekly telephone interviews from a study coordinator will be undertaken to facilitate accurate registration and compliance pain score.

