## Data Availability

Patients are coded using a numeric randomization code (anonymized), and only the principal investigators have access to this code. The source data are kept by the project leader for 15 years at the data center of the Asian Institute of Gastroenterology. All data generated or analyzed during this study will be included in the published results. Any data required to support the protocol can be supplied on request. The datasets analyzed during the current study are available from the corresponding author on reasonable request.

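### As written, sedation and repeat ESWL sessions differ between the arms, and the protocol does not settle whether the blinded principal investigator has access to the allocation code

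*Protocol article*

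**What the plan says.** All references are to the protocol article.

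**Sedation.** For active patients, Combined ESWL and endoscopic treatment states: "Once epidural anesthesia is achieved, the patient will be given a light sedation". No condition is attached. Randomization, blinding, and treatment allocation describes the sham (needle prick, machine sound, covered eyes) and then says "if the patient wishes, he or she will be given light sedation". The Sham treatment section is silent on sedation.

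**Anesthesia and sessions.** In the active arm "bupivacaine will be used to block the T6–T12 thoracic spinal segments". In the sham arm "patients will be given a transient superficial pinprick sensation to give the feeling of epidural anesthesia", and the lithotripter runs without touching the patient. If the stones are not fully cleared at the first active session, "a second session will be scheduled the following day". Neither the Sham treatment section nor the blinding section mentions a repeat sham session.

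**Who is blinded.** Patients are blinded and the operator is not; "the principal investigator and the statistician will be blinded to the treatment arms". The weekly caller and the person performing quantitative sensory testing (QST) are not mentioned there.

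**The code.** Data Availability says patients carry a numeric randomization code and that "only the principal investigators have access to this code". The blinding section places treatment codes in sealed envelopes, to be opened for one patient at a time in an emergency, with the reason recorded.

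**Outcome collection.** The primary outcome is a patient-completed VAS diary. "Weekly telephone interviews from a study coordinator will be undertaken to facilitate accurate registration".

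**The concern.** The Introduction justifies the trial by the large nonspecific effects of invasive procedures and a marked placebo response in painful chronic pancreatitis. The sham exists to make those effects equal between the arms. It can do so only if the patient's experience does not point to the arm.

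Sedation bears directly on this. A sham patient who declines it lies alert, with no sensory block and no shock-wave contact, and is better placed to notice that both are missing. A patient called back the next day for more lithotripsy has, on the text as it stands, been given a sign found only in the active arm. Both cues would most plausibly favor active treatment, because patients who believe they were treated tend to report more relief and those who suspect sham report less.

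The code is a separate matter. If the role declared blinded can look up allocations, that safeguard does not work as described. Blinding lost during conduct cannot be restored at analysis.

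**Working it through.** **1. Sedation, read both ways.**
- If the sentence in the blinding section covers sham patients only, sedation is routine in the active arm and on request in the sham arm.
- If it covers both arms, it contradicts the unconditional statement in the active-treatment section.

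Neither reading gives one consistent account. The silence of the Sham treatment section does not settle it.

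**2. Second session.** The trigger is incomplete stone clearance, which arises only where stones are being treated. The article states no corresponding event in the sham arm.

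**3. The code, read both ways.**
- Read as a pseudonymization key, the Data Availability sentence is compatible with a blinded principal investigator. It sits beside a statement on anonymized data, which favors this reading.
- Read as the allocation, it contradicts the blinding section. That section uses the word codes for treatment assignment and speaks of a code being broken, which favors this reading.

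The text does not decide between them.

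**4. What a bias of a given size would do.** The documents give no figure for it, so the shift is an assumption and a range is shown.

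Inputs from Sample size determination: difference 30%, SD 45%, 48 per group, two-sided 0.05, power 90%.

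The plan's own figure first, by the normal approximation:

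n = 2 × (1.960 + 1.282)² × (45/30)² = 2 × 10.51 × 2.25 = 47.3, rounded up to 48 per group. Power at 48 is 90.4%. The stated figure reproduces.

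Standard error of the difference in means: 45 × √(2/48) = 9.19 points.

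With no true effect and a spurious shift b, the two-sided rejection rate is Φ(b/9.19 − 1.960) + Φ(−b/9.19 − 1.960):

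| Assumed shift b (points) | b / 9.19 | Rejection rate |
|---|---|---|
| 0 | 0.00 | 5.0% |
| 5 | 0.54 | 8.5% |
| 10 | 1.09 | 19.3% |
| 15 | 1.63 | 37.2% |

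This uses the simple two-group comparison behind the sample size, not the planned mixed model. It treats the shift as the total effect of unequal expectation and does not apportion it among sedation, repeat sessions or anything else.

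**The case against.** Much can be said for the plan, and parts of it stand.

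- **Masking is not neglected.** Eyes are covered in both arms, the sham includes a needle prick and machine sound, and sham ERCP involves real passage of the endoscope. This stands. A real thoracic block against a pinprick is also a larger difference than sedation, and reconciling the sedation wording would not remove it.
- **The second session rests on silence.** The Abstract promises corresponding sham procedures, so a sham repeat may be laid down in the full protocol. This stands as a limit: the article states no counterpart, but that does not establish that none exists.
- **The code may be only an identifier.** The sequence is generated by an uninvolved biostatistician, randomization is done by a separate physician, and opening an envelope requires a signed and dated reason. These are real safeguards. A reader might infer that the principal investigator holds the allocation list, but the text does not show this. What remains is an ambiguity to be resolved.
- **Outcome staff.** A reader might infer that the weekly caller is unmasked and that blinding leaks to those collecting outcomes. The documents do not support this. They name only the operator as unblinded and do not give the status of the caller or the QST tester. An article may leave that to the full protocol, and the pain score is the patient's own entry. The same caution applies to an allocation guess: none is described, but one may be planned.

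The sedation discrepancy is untouched by any of this, because it lies between two things the article states.

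**Conclusion.** The point holds in limited form. The sedation discrepancy is documented, and under either reading the text must be reconciled. The second-session difference holds as a gap in what is stated. The principal investigator's blinding and access to the code are in tension, which clarification may resolve entirely.

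The size of any bias is unknown. The 8.5%, 19% and 37% false-positive rates show only how sensitive a trial of this size would be to assumed shifts of 5, 10 and 15 points. They do not estimate what the wording would cause. The expected direction, in favor of active treatment, is also a judgment.

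This should be corrected because it touches the purpose of the sham and costs little. It ranks below a critical defect: no actual unblinding is shown, and the article describes several masking measures that do apply.

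**What to change.** 1. Reconcile Combined ESWL and endoscopic treatment, Sham treatment, and Randomization, blinding, and treatment allocation, so that sedation and the scheduling of sessions do not reveal the arm. Which clinical rule achieves this is for the investigators to decide.
2. Reconcile the blinding section with Data Availability. Say whether the code is an identifier key or the allocation, and state that any code revealing allocation is held by someone other than the blinded principal investigator, such as the independent biostatistician.
3. As a low-cost addition, confirm that the weekly caller and the QST tester are masked, and ask patients to guess their allocation at an existing visit, reporting the answers by arm with the primary result.

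Items 1 and 2 need a wording amendment and perhaps a change in who holds the code. Item 3 needs a sentence on roles and one question at a scheduled visit. Sample size and primary analysis are unchanged. The first patient was randomized in January 2020 and recruitment was expected to run to July 2021, so an early amendment would cover most patients if recruitment was roughly even.
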